### 3.1 GENERAL DESIGN

This is a double-blind, randomised, placebo-controlled, multi-centre parallel group futility trial in patients with PD of moderate severity. The plan is to recruit and randomise 198 patients in a 1:1 ratio to receive either oral Simvastatin or matched placebo for 24 months. A one month low dose phase of 40mg daily will be followed by a 23 month high dose phase of 80mg daily and a final two month phase off trial medication. Participants will be followed up at 1 month, 6, 12, 18, 24 and 26 months ( $\pm 2$  weeks) post-baseline. Visits to obtain outcome measures are undertaken face-to-face, and can be either in an outpatient clinic or at home.

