### 3.3 ANALYSIS POPULATIONS

We will base the primary analysis of the primary outcome on a modified intention-to-treat (mITT) principle. The mITT evaluable sample for the primary analysis will include all participants who are randomised, provide baseline outcome data, commence to the higher dose phase of the study and provide 24-month outcome data. Imputation will only be performed for missing questionnaire items that fulfil pre-specified criteria as outlined in section 4.10.

To investigate any effect of compliance with taking study medication, if  $\geq 20\%$  of participants in the active Simvastatin group are identified as non-compliers (according to each of the definitions in section 4.4.2), we will undertake additional sensitivity analyses of the primary outcome (further details in section 7.3.1). This population will consist of all participants with baseline and 24-month primary outcome data.

The safety population will consist of all participants who have at least one dose of allocated trial treatment.

A washout period has been included in the study design to explore the potential disease-modifying effect of Simvastatin. Trial treatment will be discontinued at 24 months and a follow-up visit is conducted two months later at 26 months post-baseline. All participants still on trial treatment at the higher dose of 80mg at 24 months with valid baseline, 24 and 26 months data will be included in the disease-modifying analysis.

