### **3.4.2 Exclusion Criteria**

Potential participants meeting any of the following criteria will be excluded from study participation:

- Diagnosis, or suspicion, of other cause for parkinsonism
- Known abnormality on CT or MRI brain imaging considered to be causing symptoms or signs of neurological dysfunction, or considered likely to compromise compliance with study protocol
- Concurrent dementia defined by MoCA score  $< 21$
- Concurrent severe depression defined by MADRS score  $> 31$
- Prior intracerebral surgical intervention for PD including deep brain stimulation, lesional surgery, growth factor administration, gene therapy or cell transplantation
- Already actively participating in a research study that might conflict with this trial
- Prior or current use of statins as a lipid lowering therapy
- Intolerance to statins
- Untreated hypothyroidism

- End stage renal disease (creatinine clearance < 30 mL/min) or history of severe cardiac disease (angina, myocardial infarction or cardiac surgery in preceding two years)
- Estimated Glomerular Filtration rate (eGFR) < 30 mL/min
- History of alcoholism or liver impairment
- Creatine kinase (CK) > 1.1 x upper limit of normal (ULN)
- Aspartate transaminase (AST) or alanine transaminase (ALT) > 1.1 x ULN
- Females who are pregnant or breast feeding or of child-bearing potential and unwilling to use appropriate contraception methods whilst on trial treatment
- Currently taking any medication contraindicated with Simvastatin use (Appendix 2 of the protocol v4.5)
- Any requirement for statin use
- Regular participation in endurance or high-impact sports
- Unable to abstain from consumption of grapefruit-based products

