Hence  $\alpha$  and  $\beta$  were chosen to reflect the futility design-based hypotheses, with the one-sided  $\alpha$  set at 10% and  $\beta$  at 20% (i.e. 80% power).

Based on a recently reported study at the time of the design of this futility trial, the expected mean increase in MDS-UPDRS part III from baseline to 12 months in the placebo group is assumed to be 2.2 points, with corresponding standard deviation of 7.3 points. Assuming that this increase in MDS-UPDRS part III is linear over time, gives an expected mean increase from baseline to 24 months of 4.4 points in the placebo group (i.e.  $\mu_p = 4.4$ ). Therefore, if we assume the MCID is -3, this implies the mean of the Simvastatin group,  $\mu_s$ , is 1.4 points. Additionally, we assume a slightly inflated standard deviation over this period of 7.5 points.

The sample size calculation was based on a two-sample t-test with a 10% one-sided alpha. Following the previously listed assumptions, the number of participants needed to follow-up at 24 months (i.e. with primary outcome data) is 57 participants per group, to provide 80% power to reject the null hypothesis of non-futility and declare futility.

This sample size was inflated to allow for a proportion of participants allocated to the Simvastatin group to stop taking the trial medication during the initial 1-month low dose phase. Assuming that this proportion was 15%, the above sample size was inflated by  $(1-0.15)^{-2}$ , to give 79 participants per group. Secondly, the sample size was adjusted to allow for a (non-differential) loss to follow-up rate of 20%. Accordingly, the sample size was further inflated by a factor of  $(1-0.2)^{-1}$ , to give a sample size of 99 participants per group and a total recruitment target of 198 participants commencing the higher dose phase of the study.

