## **9 SAFETY DATA**

---

Adverse event (AE) data gathered from telephone contacts and visits of participants included in the safety population will be used to determine the safety and tolerability of Simvastatin.

The number and percentage of adverse events (AEs) will be reported by participant's completion status (i.e. completed IMP, discontinued IMP and withdrew) and by treatment taken (i.e. placebo, 40mg only or 80mg). We will also report information on:

- Timing of withdrawal/discontinuation
- Severity of AEs prior to withdrawal/discontinuation
- Classification of AEs prior to withdrawal/discontinuation
- Whether the decision to withdraw/discontinue was blinded.

We will report summary statistics of AEs by treatment taken, and if the number of participants reporting at least one AE within an organ system classification exceeds 5% of the safety population, we will report the AE summary statistics by treatment taken for that particular organ system. The summary statistics of serious adverse events (SAEs) will be reported by treatment taken and organ system classification.

Any AEs and/or SAEs which are related to common known effects side of statins use, as listed in the BNF , will be reported by treatment taken. These include:

- Asthenia
- Constipation
- Diarrhoea
- Dizziness
- Flatulence
- Gastrointestinal discomfort
- Hepatitis
- Headache
- Myalgia
- Myopathy (including myositis)
- Nausea
- Sleep disorder
- Thrombocytopenia

The summary statistics of AEs and SAEs will include:

- Numbers and percentages of participants reporting at least one AE
- Numbers and percentages of participants reporting AEs by the total number of AEs participants have reported
- Numbers and percentages of participants reporting at least one SAE
- Numbers and percentages of participants reporting SAEs by the total number of SAEs participants have reported

In addition, we shall produce Kaplan-Meier curves of cumulative incidences of AEs and SAEs by treatment taken.

Although no formal hypothesis testing of the safety data will be conducted, 95% confidence intervals of proportions by treatment taken will be presented. Any notable increase in safety related events within the Simvastatin groups (40mg only or 80mg) compared to the control group will be investigated further.

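### SAP section 9 guarantees an organ-class table by treatment taken only above a pooled 5% threshold, so a non-serious excess of up to about 9% v 0% outside the statin-related effects can go untabulated

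*SAP*

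**What the plan says.** Section 9 of the SAP sets the rule for AE tables by organ system. The trigger is "if the number of participants reporting at least one AE within an organ system classification exceeds 5% of the safety population". When it is met, "we will report the AE summary statistics by treatment taken for that particular organ system". The denominator comes from section 3.3: "The safety population will consist of all participants who have at least one dose of allocated trial treatment". Nothing divides it by treatment.

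The same section provides several reports that do not depend on this threshold:

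- AE summaries by treatment taken (placebo, 40mg only, 80mg), not broken down by organ class.
- Serious adverse events (SAEs) by treatment taken and organ class.
- Any AE or SAE related to known statin effects in the BNF, by treatment taken. Thirteen terms are named as included.
- Kaplan-Meier curves of AEs and SAEs by treatment taken.
- The classification and severity of AEs before withdrawal or discontinuation. A split by treatment is not stated.

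The section closes with an undertaking: "Any notable increase in safety related events within the Simvastatin groups (40mg only or 80mg) compared to the control group will be investigated further". It gives no criterion for a notable increase and attaches no table to it.

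**The concern.** A harm caused by the drug appears in the simvastatin participants and not on placebo. With equal arms, a threshold on the pooled population roughly halves the apparent frequency of such an excess, so the rule is least sensitive to the pattern that a safety comparison is meant to find. A class can fall below 5% overall while nearly all its events are on one treatment.

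Confirming safety and tolerability is secondary objective (i) in section 2.2, and section 7.2.1 says that the final decision on futility should also take the safety analysis into account. The BNF route covers expected harms. For unexpected non-serious harms, the organ-class table is the plan's main display, and the threshold applies to that table.

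**Working it through.** **Inputs.** The threshold is strictly more than 5% of the safety population (section 9), which is everyone with at least one dose (section 3.3). For size, section 3.1 says "The plan is to recruit and randomise 198 patients in a 1:1 ratio to receive either oral Simvastatin or matched placebo for 24 months", while section 4.2 speaks of "a total recruitment target of 198 participants commencing the higher dose phase of the study". The number dosed is therefore not fixed by the SAP and is an assumption below.

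**The plan's own figure.** For a difference of 3, SD 7.5, one-sided alpha 10% and 80% power, the normal formula gives 56.35 per group, rounded up to 57 (exact t-test power 0.801). Then 57/0.85² = 78.9, so 79; 79/0.8 = 98.75, so 99; and 2 × 99 = 198. The sample size reproduces.

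**Largest count below the threshold at 198.** 0.05 × 198 = 9.9. Nine affected participants do not exceed this; ten do.

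**How uneven nine can be.** With 99 per arm, two-sided Fisher exact tests, unadjusted:

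| Simvastatin v placebo | Rates | p |
|---|---|---|
| 9 v 0 | 9.1% v 0% | 0.003 |
| 8 v 1 | 8.1% v 1.0% | 0.035 |
| 7 v 2 | 7.1% v 2.0% | 0.17 |
| 6 v 3 | 6.1% v 3.0% | 0.50 |

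For 9 v 0 the Newcombe 95% interval for the difference is 3.4 to 16.4 percentage points.

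**Sensitivity to the assumed size** (1:1, every affected participant in one arm):

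| Dosed | 5% of total | Largest count below threshold | Rate in one arm | p |
|---|---|---|---|---|
| 168 | 8.4 | 8 of 84 | 9.5% | 0.007 |
| 180 | 9.0 | 9 of 90 | 10.0% | 0.003 |
| 198 | 9.9 | 9 of 99 | 9.1% | 0.003 |
| 220 | 11.0 | 11 of 110 | 10.0% | 0.0008 |
| 234 | 11.7 | 11 of 117 | 9.4% | 0.0008 |

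The upper end corresponds to 198 starting the higher dose after 15% have stopped in the low-dose phase: 198/0.85 = 232.9. The worst case stays between 9.1% and 10.0% throughout.

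**The plan's own groups.** Reporting is by treatment taken, not by randomised arm. If 15 of the 99 on simvastatin took 40mg only (an assumption of about 15%), nine events all on 80mg would be 9/84 = 10.7% v 0/99, p=0.0007, and still below the threshold.

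**Whether another report would show it.** SAEs and BNF-related effects are reported at any frequency, so the gap is confined to other, non-serious events. Overall AE summaries and Kaplan-Meier curves count those events but do not say which organ class they belong to. The classification of AEs before stopping covers only participants who stop.

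**The case against.** The strongest reply is that little is lost. Serious events and any AE related to known statin effects are reported by treatment taken however rare they are. The undertaking to investigate is not limited to tabulated classes, the statisticians hold all the AE data, and the threshold sets a minimum for reporting without forbidding more. The figure of 9 v 0 is the extreme of the possible splits. It presupposes almost no placebo events in a whole organ class over 24 months, and it is an unadjusted p-value in a section that plans no formal testing of safety data.

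Most of this stands, and it limits the point. A reader might infer that an excess of this size is never shown by treatment. The SAP does not support that: an excess made up of BNF-related effects would be shown. Nor does it follow that an investigation could not start; the text leaves it possible but ensures no display that would prompt it.

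A reader might also infer that raised CK, raised AST/ALT and renal events are left out. They are not among the 13 named terms, although section 3.4.2 excludes patients on CK, on eGFR and on "Aspartate transaminase (AST) or alanine transaminase (ALT) > 1.1 x ULN". But the named terms are given as examples and include hepatitis and myopathy, and the wording reaches events related to known effects. Whether laboratory or renal events fall within it depends on the BNF list, which the SAP does not reproduce in full. Their omission cannot be claimed.

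What the reply does not remove is that, followed as written, the plan does not commit to showing an imbalance in a class below the threshold.

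**Conclusion.** The point holds in limited form. The organ-class table by treatment taken is guaranteed only when more than 5% of all dosed participants are affected. At an assumed 198 dosed, a one-sided excess of up to 9 v 0 (9.1% v 0%) in non-serious events outside the BNF-related effects is not tabulated by treatment at organ-class level. The worst case is 9.1% to 10.0% for 168 to 234 dosed at 1:1. At 198, only 9 v 0 and 8 v 1 reach nominal significance; more even splits below the threshold would not stand out.

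The primary analysis is unaffected. This is a reporting weakness bearing on secondary objective (i), worth correcting because the correction is cheap.

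**What to change.** In section 9, remove the pooled 5% condition. Tabulate the number and percentage of participants with at least one AE by treatment taken (placebo, 40mg only, 80mg) for every organ system class, in a supplement if the table is long. Add a sentence saying whether reported CK, AST/ALT and renal events count as BNF-related effects.

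Moving the 5% threshold to each treatment group is less suitable. The 40mg-only group may be small, and one event among 20 participants is already 5%.

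The cost is SAP wording and a few more table rows, some with small counts that need cautious reading. No new data are needed.

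### Section 9 gives AEs and SAEs a confidence interval for each group's own proportion but no between-group estimate, so the promised comparison with control rests on undefined judgement

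*SAP*

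**What the plan says.** SAP section 9 reports AEs and SAEs as counts and percentages, with Kaplan-Meier curves. The grouping is "by treatment taken (i.e. placebo, 40mg only or 80mg"), so there are three groups defined by what was taken rather than two defined by allocation. On uncertainty and comparison, two consecutive sentences matter:

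- The first rules out formal tests of safety and then fixes the only interval: "95% confidence intervals of proportions by treatment taken will be presented".
- The second turns to the comparison between groups: "Any notable increase in safety related events within the Simvastatin groups (40mg only or 80mg) compared to the control group will be investigated further".

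The population, from section 3.3: "The safety population will consist of all participants who have at least one dose of allocated trial treatment". Its expected size is not given.

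Other outcomes are handled differently. Table 3 in section 8.1 labels diabetes incidence and the cholesterol measures as addressing the safety of simvastatin. Section 8.2 gives these group differences with two-sided 95% intervals, reported as exploratory and without multiplicity adjustment.

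**The concern.** The planned output does not answer the question that section 9 itself asks. An increase compared with control is a statement about a difference, and its uncertainty is that of the difference. Two separate intervals describe each group's rate. They show neither the size of the excess nor how precisely it is known, and comparing them by eye is not equivalent to an interval for the difference.

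With *notable* undefined, two careful readers could reach opposite conclusions from the same table, and neither would have departed from the plan.

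Safety and tolerability is secondary objective (i) in section 2.2, and section 7.2.1 says the final decision on futility should also weigh the safety analysis. The primary futility test is not affected.

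**Working it through.** **1. Group size.** Section 9 gives neither group sizes nor event rates. The only sizes come from the design. Section 3.1: "The plan is to recruit and randomise 198 patients in a 1:1 ratio". Section 4.2: "with the one-sided $\alpha$ set at 10% and $\beta$ at 20% (i.e. 80% power"), a margin from "if we assume the MCID is -3", and SD 7.5. Reproducing the plan's figure:

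- n per group = 2 × (1.2816 + 0.8416)² × 7.5² / 3² = 56.35, rounded up to 57. Two-sample t power is 80.1% at 57 and 79.6% at 56.
- Early stopping: 57 / 0.85² = 78.9, giving 79.
- Loss to follow-up: 79 / 0.8 = 98.75, giving 99 per group, 198 in total.

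These figures reproduce. I take 99 per arm as an **assumption** for safety. Section 4.2 counts the 198 as starting the higher dose phase, so the number dosed could be larger. As a variant I use 85 against 99, assuming about 15% do not reach 80mg.

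**2. What non-overlap means.** With equal standard errors SE, two 95% intervals separate when the difference exceeds 2 × 1.96 × SE. The difference has standard error √2 × SE, so z = 2 × 1.96 / √2 = 2.77 and two-sided p = 0.0056.

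**3. One worked case: 22/99 on simvastatin, 10/99 on placebo** (22.2% and 10.1%).

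- Wilson interval: [p + z²/2n ± z√(p(1−p)/n + z²/4n²)] / (1 + z²/n), with z = 1.96. This gives 15.2% to 31.4% and 5.6% to 17.6%, which overlap.
- Newcombe interval for d = p₁ − p₀: lower limit d − √[(p₁−l₁)² + (u₀−p₀)²], upper limit d + √[(u₁−p₁)² + (p₀−l₀)²], where l and u are the Wilson limits.
- Lower: 0.121 − √(0.071² + 0.075²) = 0.018. Upper: 0.121 + √(0.091² + 0.045²) = 0.223.
- The difference is 12.1 points, 95% CI 1.8 to 22.3.

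**4. Smallest simvastatin count at which each reading shows an excess (99 v 99).**

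| Placebo count | Difference CI excludes 0 | Wilson intervals separate | Clopper-Pearson intervals separate |
|---|---|---|---|
| 5 | 14 | 18 | 19 |
| 10 | 20 | 25 | 26 |
| 20 | 33 | 38 | 39 |
| 30 | 44 | 50 | 51 |

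**5. Chance of flagging, by exact binomial enumeration.** All event rates are assumed.

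| True rates, placebo v simvastatin | Arms (simvastatin v placebo) | Difference CI | Non-overlap, Wilson | Non-overlap, Clopper-Pearson |
|---|---|---|---|---|
| 5% v 15% | 99 v 99 | 65% | 34% | 28% |
| 10% v 20% | 99 v 99 | 51% | 21% | 17% |
| 10% v 25% | 99 v 99 | 81% | 52% | 45% |
| 20% v 35% | 99 v 99 | 66% | 34% | 29% |
| 10% v 20% | 85 v 99 | 48% | 18% | 14% |
| 20% v 35% | 85 v 99 | 65% | 32% | 28% |

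**6. The other direction.** Suppose *notable* is read as any numerically higher proportion. With equal true rates of 10% and 99 per arm, an excess is flagged 45% of the time. The lower limit of the difference CI lies above zero in about 2%.

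**The case against.** **The overlap rule is not in the SAP.** A reader might infer from step 5 that harms will be under-called, or that about half of real excesses will be missed. The document does not support that. Section 9 names no overlap criterion; it prompts follow-up by an undefined judgement, and step 6 shows that another plausible reading over-calls. This objection stands. It removes any claim about the direction or size of the error, but not the point that the plan supplies no comparison.

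**The safety groups are not two arms of 99.** This also stands. If 15 people took 40mg only (assumed) and 99 took placebo, non-overlap corresponds to p = 0.011, and even the difference CI flags 20% v 35% only about 28% of the time. The illustration does not carry over to that group. It was also formed after randomisation, partly by tolerability, so its contrast with placebo is not randomised.

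**Not all safety outcomes are affected.** Correct: diabetes and cholesterol get group differences with intervals in section 8.2. The point is confined to AEs and SAEs.

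**Describing harms without testing is legitimate, and a reader can compute the difference from the counts.** The first part stands; avoiding formal tests is no error here. But a risk difference with its interval is estimation, as the per-group intervals are, and leaving the comparison to readers does not meet the SAP's own commitment to look for an increase.

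**More intervals bring chance findings.** True. Over the 13 listed statin effects with no real harm, up to 1 − 0.975¹³ = 28% of trials would show at least one lower limit above zero (independence and 2.5% each assumed). That argues for a caveat beside the table, not for omitting the estimate.

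**Conclusion.** The point holds in a limited form. For AEs and SAEs, section 9 commits to looking for an increase against control but plans only within-group intervals and leaves *notable* undefined. The comparison can be mis-called either way, and the document fixes neither the direction nor the extent.

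The 34% against 66% for a true 20% v 35% shows how far the reading rule can matter. It depends on an assumed 99 per arm, assumed event rates, Wilson intervals and a non-overlap rule that the SAP does not state. It is not an estimate of what this trial will miss. This is a worthwhile, inexpensive improvement to the reporting of a secondary objective.

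**What to change.** In section 9:

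1. Keep the per-group 95% intervals, which show the uncertainty of each absolute rate.
2. Add the risk difference with a 95% CI (Newcombe, for example) for at least one AE, at least one SAE, each listed statin effect and each organ class shown.
3. Name the contrast. Make all simvastatin versus placebo the main one. If 80mg versus placebo and 40mg only versus placebo are also shown, label them descriptive and non-randomised.
4. Say that a notable increase will be judged from these differences and their intervals, and state in advance what size or pattern prompts further investigation.
5. Keep the statement that no formal tests are done.

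The cost is SAP wording and a table column per contrast, with no new data. The drawback is more intervals to read without multiplicity control; say so beside the table.

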## APPENDIX

### A. ADDITIONAL INFORMATION FOR OUTCOME MEASURES

| PD Medication               | Conversion Factor |
|-----------------------------|-------------------|
| Amantadine                  | 1                 |
| Apomorphine                 | 10                |
| Azilect                     | 10                |
| Bromocriptine               | 10                |
| Cabergoline                 | 80                |
| Duodopa                     | 1.11              |
| Entacapone                  | 0.33*             |
| Levodopa dispersible        | 1                 |
| Levodopa immediate release  | 1                 |
| Levodopa controlled release | 0.75              |
| Lisuride                    | 100               |
| Madopar                     | 1                 |
| Mirapex                     | 100               |
| Opicapone                   | 0.5*              |
| Pergolide                   | 100               |
| Pramipexole                 | 100               |
| Rasagiline                  | 100               |
| Requip                      | 20                |
| Ropinirole                  | 20                |
| Rotigotine                  | 30                |
| Rytary                      | 0.6               |
| Safinamide                  | 100**             |
| Selegiline Oral             | 10                |
| Selegiline Sublingual       | 80                |
| Sinemet                     | 1                 |
| Sinemet controlled release  | 0.75              |
| Stalevo                     | 0.33*             |
| Tolcapone                   | 0.5*              |

\* Multiply immediate release levodopa dose by conversion factor and add to immediate release levodopa dose.

\*\* Add this value to the LED, regardless of dose.

Table 4: Conversion factors for levodopa-equivalent dose

Example: Immediate release Levodopa dose = 400 and Entacapone = 800, implies:

$$\text{LED} = (1 \times 400) + (0.33 \times 400) = 400 + 132 = 532$$

| Secondary outcome | Missing Items                                                                                                                                                                                                                                                                                                                                                                                                                                                                                                                                                                                                                                                                                                                                                                                                                                                                                  |
|-------------------|------------------------------------------------------------------------------------------------------------------------------------------------------------------------------------------------------------------------------------------------------------------------------------------------------------------------------------------------------------------------------------------------------------------------------------------------------------------------------------------------------------------------------------------------------------------------------------------------------------------------------------------------------------------------------------------------------------------------------------------------------------------------------------------------------------------------------------------------------------------------------------------------|
| MDS-UPDRS part II | Goetz, et al. 
Imputation formula
$D = \frac{A \times B}{C}$                                                                                                                                                                                                                                                                                                                                                                                                                                                                                                                                                                                                                                                                                                                                                                                                                |
| MDS-UPDRS Total   | 
 
▪ A - sum of the items scored,
 
▪ B - total number of items which should have been scored
 
▪ C - number of items with actual score
 
▪ D - imputed score.
 
 
Part I missing a maximum of 1 item, part II missing maximum of 2 items, part III missing maximum of 3 items, part IV cannot have any missing items.
                                                                                                                                                                                                                                                                                                                                                                                                                                                                      |
| MDS-UPDRS part IV | 
For questions 1, 3 and 6, the score is based on the percentage reported in part C of each question, which is calculated by dividing the number of hours stated in part B by the number of hours stated in part A and multiplying by 100. For each of questions 1, 3 and 6, the question score is then:
 
 
• 0 if part B = 0
 
• 1 if part C ≤ 25%
 
• 2 if part C is 26-50%
 
• 3 if part C is 51-75%
 
• 4 if part C > 75%.
 
 
In instances where the ordinal score is missing but part C (the percentage) is available, the score will be determined based on the above thresholds of the reported part C. If the ordinal score and part C are missing but part A and B are available, part C (the percentage) will be calculated and the ordinal score determined by the above defined thresholds.
 |
| MADRS             | 
For a maximum of 1 missing item
 
Use weighted means from Gale and Hawley  to calculate total MADRS score, see Table 6 for weights.
                                                                                                                                                                                                                                                                                                                                                                                                                                                                                                                                                                                                                                                                                                                                   |
| ACE-III           | Participants with any missing items set total score to missing (approach 3, Lees, et al.  ).                                                                                                                                                                                                                                                                                                                                                                                                                                                                                                                                                                                                                                                                                                                                                                                      |
| PDQ-39            | Use EM algorithm but requires more than 200 participants  .                                                                                                                                                                                                                                                                                                                                                                                                                                                                                                                                                                                                                                                                                                                                                                                                                       |

Table 5: Methods for handling missing items for questionnaire data, where available

| Item | Weight |
|------|--------|
| 1    | 1.03   |
| 2    | 1.14   |
| 3    | 1.13   |
| 4    | 1.20   |
| 5    | 0.69   |
| 6    | 1.18   |
| 7    | 1.15   |
| 8    | 1.11   |
| 9    | 0.89   |
| 10   | 0.47   |

*Table 6: Item weights for the calculation of MADRS given one item is missing*

